## Abstract

**Background:**

Autism spectrum disorder (ASD) is a neurodevelopmental condition characterized by repetitive stereotypical behavior and communication deficits. Currently, it lacks a specific clinical treatment method. Pediatric Tuina is a recent therapy in traditional Chinese medicine (TCM) and has been used to treat children with ASD. Nonetheless, it remains uncommon given the lack of large-scale evidence-based medical studies. This study aims to compare the efficacy of Tuina and conventional treatment in children with ASD.

**Methods:**

Eligible children will be randomly assigned to either the pediatric Tuina plus conventional treatment group or to the conventional treatment alone group based on a random table at a ratio of 1:1. The effectiveness of the Tuina intervention for ASD will be evaluated by a third-party organization. The pre- and post-intervention scores on the Childhood Autism Rating Scale comprised the primary outcome, whereas pre- and post-intervention scores on the Autism Treatment Evaluation Checklist were the secondary outcomes to assess improvement in symptoms. Baseline values of the participants will be determined at the time of registration. Outcomes will be evaluated after the 30th treatment session. The follow-up period will last for 6 months after treatment.

**Discussion:**

This study will evaluate the effectiveness and safety of Tuina in the treatment of ASD. The results of this study could provide reliable evidence to improve the management of patients with ASD.

**Trial registration:**

Chinese Clinical Trial Registry (*CHICTR*), ChiCTR2000040452. Registered on 28 November 2020.

## Background

Autism spectrum disorder (ASD) is a neurodevelopmental disorder characterized by typical repetitive behaviors and communication difficulties [1]. It has a childhood onset, and patients with this condition have lifelong difficulties with social interaction, communication, and sensory perception [2]. The etiology of ASD involves complex and polygenic interactions as well as possible environmental factors [3]. ASD is a serious public health problem worldwide, with its high morbidity and disability rates garnering increasing attention. Based on the epidemiological studies, the incidence rate of ASD is > 1–2% [4].

However, there are no specific agents for the treatment of ASD, which is currently treated with behavioral interventions such as early parent-mediated interventions [5–8]; naturalistic behavioral developmental interventions; behavioral and social treatments for school-age children, adolescents, and adults [9–12]; and even medical clown interventions [13]. These clinical interventions can significantly improve the social adaptability of children with ASD.

Clinical treatment of ASD using evidence-based pharmacology is limited to treating the co-occurring behavioral problems caused by mental illness rather than ASD itself. Risperidone [14–17] and aripiprazole [14, 18, 19] have been approved by the Food and Drug Administration to improve irritability or restlessness in children and adolescents with ASD. However, both drugs can cause adverse effects, including sedation and weight gain after long-term use, which increases the risk of subsequent health problems [19].

To alleviate the clinical symptoms of ASD and to save medical costs, traditional therapies have been used in the treatment of ASD with numerous advantages.

Tuina is an important and effective external treatment in improving stunting [20] and decreasing physical and mental tension [21], among other benefits. Currently, some Tuina manipulations have been applied as interventions for children with ASD [22, 23] with a certain degree of success [24]. Qigong Tuina, which is a specific Tuina intervention in children with ASD [25, 26], has been shown to improve the symptoms of children with ASD.

Pediatric Tuina is a traditional Chinese medicine (TCM) therapy that acts on specific acupoints on the hands, back, and arms [27], including Wujing acupoints for different fingers. These acupoints target the spleen, liver, heart, lung, and kidney based on the meridian and collateral theory. The order is located on the thread surface of the five fingers in children (the spleen acupoint is located on the thumb). Stimulating different acupoints by specific manipulations has various curative effects.

However, there is no strong evidence regarding the single-use of pediatric Tuina intervention for ASD treatment [28]. The two objectives of this study are (1) to further evaluate the effectiveness of pediatric Tuina as a complementary therapy for children with ASD aged 2–6 years, by comparing it with conventional treatment through a standardized clinical study design, and (2) to promote and facilitate the use of pediatric Tuina in ASD by allowing more children with ASD to benefit from Tuina as a healthy and environmentally friendly physical therapy.

## Methods/design

### Study design

This will be a randomized controlled trial. To meet ethical requirements and considering the particularity of ASD, this study will not employ a blind design. The trial will be conducted at Hunan University of Chinese Medicine, China, from November 2020 to December 2022. Eligible children will be randomly divided into the pediatric Tuina plus conventional treatment group or the conventional treatment group based on a computer-generated random table at a ratio of 1:1. Efficacy will be assessed using the Childhood Autism Rating Scale (CARS) and the Autism Treatment Evaluation Checklist (ATEC). Before study commencement, all participants will be assessed using a scale by a third party not involved in the study. The baseline level of the participants will be determined at the time of enrollment; further, the participants will be evaluated again after the 30th treatment, with a follow-up period of 6 months postoperatively. Figure 1 shows the flowchart of the study.

**Fig. 1 Fig1:**
[figure not shown]
Flowchart of the study. A total of 400 participants will be randomized to the two groups. The interventions will last for 25 min and will be conducted two times per week for 6 weeks, and a 6-month follow-up was performed after treatment. The main efficacy score will be based on the CARS, and the secondary outcome indicators will be evaluated using the ATEC. CARS, Childhood Autism Rating Scale; ATEC, Autism Treatment Evaluation Checklist

### Participants

This study will recruit 400 children with ASD from autism organizations certified by the Hunan Disabled Persons' Federation, including Xingxueyuan Education Development Center (Tianxin District, Changsha City), Aimeng Rehabilitation Center for Special Children (Yuhua District), and Vitality Autism Rehabilitation Center (Yuelu District), among others.

### Eligibility criteria

#### Inclusion criteria

1. Diagnosis made by a psychiatrist based on the diagnostic criteria for ASD of the Diagnostic and Statistical Manual of Mental Disorders (DSM-5)

2. Age: 2–6 years old

3. CARS score ≥ 30 points

4. The guardian of the child is informed of the study and the child is compliant with the treatment cycles

5. No history of participation in other observational studies or unplanned interventions within the past 30 days, such as acupuncture and herbal treatment that may affect the study results

6. No history of other serious diseases that may affect the outcomes, including organic pathologies, coagulation disorders, congenital heart disease, and epilepsy

7. No history of chronic or acute infections, such as pneumonia

8. No history of other psychiatric disorders, such as ADHD

#### Exclusion criteria

1.Children who are resistant to the Tuina intervention, with persistent crying and inability to adapt

Children who during the study develop conditions like phlebitis, open wounds, and skin breakdown in the manipulated area

#### Elimination criteria

1. Children who do not complete 30 intervention sessions following the research protocol

2. Children who received other interventions that may affect the study results

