#### Drop-out criteria

1. Children experiencing adverse events during the trial, such as pneumonia and skin disease, and who could not adhere to the Tuina therapy.

2. Children whose guardian perceived the treatment as ineffective and therefore terminated the treatment.

3. Children withdrawing from the treatment at the original rehabilitation institution or after being transferred to a different rehabilitation institution.

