#### Safety assessment

Although pediatric Tuina is a nature-based approach to healing without side effects, some adverse events (AEs) may occur during the treatment process due to medical errors. Skin damage is the most common AE during Tuina. To prevent AE occurrence, strict monitoring will be conducted. In the case of AEs, the researchers will record the time and severity of the AE and promptly deal with it.

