## Study limitations

First, the diagnosis of ASD will not be made using the Autism Diagnostic Interview-Revised or Autism Diagnostic Observation Scale due to copyright restrictions; instead, the DSM-5 will be used.

Regarding the evaluation, there are no objective biomarkers for evaluating the efficacy of ASD treatments. This study will employ a scale to evaluate the efficacy of the ASD treatment, which may lead to subjective errors.

Additionally, it is impossible to blindly perform Tuina therapy. Furthermore, the standardization of Tuina techniques and stimulation amount varies from person to person. There will inevitably be some differences in specific operations. To reduce such errors, only Tuina therapists with rigorous training and professional qualifications will participate in the study to ensure standard treatment.

Finally, given the ethical requirements, it is not possible to prohibit all children from participating in other educational or behavioral interventions. Therefore, a single Tuina intervention trial is insufficient to evaluate its feasibility for clinical application.

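### Exclusion and elimination rules that act after randomisation should not decide who is analysed: on the plain reading they remove children, mainly from the Tuina arm, and are likely to favour Tuina if those children fare worse

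*Protocol article*

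**What the plan says.** The protocol article has three lists that act on children already in the trial.

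- **Exclusion criteria:** "Children who are resistant to the Tuina intervention, with persistent crying and inability to adapt" and "Children who during the study develop conditions like phlebitis, open wounds, and skin breakdown in the manipulated area".
- **Elimination criteria:** "Children who do not complete 30 intervention sessions following the research protocol" and "Children who received other interventions that may affect the study results".
- **Drop-out criteria:** children with adverse events "who could not adhere to the Tuina therapy"; "Children whose guardian perceived the treatment as ineffective and therefore terminated the treatment"; and children who leave or change their rehabilitation institution.

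Under Allocation, children are randomised once their baseline assessment is complete. No trial period of Tuina before randomisation is described. Statistical analyses names the t-test and the rank-sum test, two-sided at 5%. It does not say that excluded or eliminated children stay in the comparison.

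**The concern.** Randomisation makes the two arms comparable at the moment of allocation. A rule that removes children for something that happens later keeps that comparability only if it acts alike in both arms or is unrelated to outcome. Several of these rules depend on contact with Tuina, so they do not act alike.

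Children who cannot tolerate the sessions, or who do not finish the course, may plausibly be those who improve less. Taking them out of one arm raises that arm's mean CARS improvement even if Tuina does nothing. If they are also not rated once eliminated, no later analysis can recover the randomised comparison.

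**Working it through.** **Step 1. When each rule acts, and on whom.**

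| Rule | When it can be seen | Arm it can reach |
|---|---|---|
| Exclusion 1: resists Tuina | In practice once Tuina is given, as no run-in is described | Tuina |
| Exclusion 2: skin or vein condition in the treated area | During the study, as stated | In practice Tuina; controls have no treated area |
| Elimination 1: fewer than 30 sessions | After allocation | Most clearly Tuina; controls on one reading |
| Elimination 2: other interventions | During the trial | Either |
| Drop-out 1: adverse event, cannot keep to Tuina | After allocation | Tuina |
| Drop-out 2: guardian sees no effect | After allocation | Either; no arm is named |
| Drop-out 3: leaves or changes institution | After allocation | Either |

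Of the four exclusion and elimination rules, two reach only the Tuina arm on any reading, and three do if the 30-session rule means Tuina sessions. With the drop-out rules added, the count is three or four of seven.

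**Step 2. What elimination means.** It has its own heading, apart from drop-out. If it only recorded that a child stopped, the drop-out list would already serve. The plain reading is therefore that the child is removed.

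**Step 3. How much it could matter.** The article gives no figure for eliminations, so there is nothing of its own to reproduce here.

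Inputs from Sample size estimation: SD 4.43, 200 children per arm, and a 10% shedding rate, borrowed here as one removal rate. Assumptions, not document figures: removal only from the Tuina arm, a fraction q removed, and a gap g in improvement between removed and remaining children. There is no true treatment effect, and the SD is held at 4.43.

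The full-arm mean equals the remaining children's mean minus q × g, so removal shifts the Tuina mean by

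bias = q × g.

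SE = 4.43 × √(1/n_T + 1/200), with n_T = 200 × (1 − q).

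Two-sided error = P(|Z + bias/SE| > 1.96).

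- **q = 10%, g = 3:** n_T = 180; bias = 0.10 × 3 = 0.3; SE = 4.43 × √(1/180 + 1/200) = 0.455; ratio 0.66; error 0.101.
- **q = 20%, g = 2:** n_T = 160; bias = 0.4; SE = 4.43 × √(1/160 + 1/200) = 0.470; ratio 0.85; error 0.136.
- **q = 20%, g = 3:** bias = 0.6; SE = 0.470; ratio 1.28; error 0.248.
- **g = 0:** bias = 0; error 0.05 at any q.

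**Step 4. Cross-check by another mechanism.** Children in the lowest fraction q on a trait that correlates ρ with CARS improvement are removed from the Tuina arm. The bias is 4.43 × ρ × φ(c)/(1 − q), where c is the q-quantile of the standard normal distribution and φ its density. For q = 10% this is 0.26 points at ρ = 0.3 and 0.43 at ρ = 0.5. In 10,000 simulated null trials the rate of false wins for Tuina was 8.6% and 15.8%, against a nominal 2.5%. At ρ = 0 it stayed at about 2.5%.

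**The case against.** The strongest reply is that the article never says outright that eliminated children leave the analysis. It names tests and no analysis population, and a condensed article may leave that to a fuller document. This stands as a limit: removal is the plain reading, not explicit text. It does not clear the criteria, because a later promise to analyse everyone would have to be reconciled with rules that exclude and eliminate the same children.

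A reader might infer more than the article supports:

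- **That most of the rules are Tuina-only.** The 30-session rule speaks of intervention sessions, not Tuina sessions. Controls have five sessions a week of each training; over 6 weeks, 5 × 6 = 30 of each type. The Interventions section gives controls no explicit duration, so neither reading is certain.
- **That children judged not to be improving leave only the Tuina arm.** The rule on perceived ineffectiveness names no arm. In an open-label trial, guardians of control children could invoke it too, which could offset or reverse the direction.
- **That adverse events are lost.** Safety assessment says "Skin damage is the most common AE during Tuina", so the expected harm is itself a ground for exclusion. But the time and severity of events are to be recorded, and Ancillary and post-trial care has them reported to the ethics committee. Only the place of these children in the adverse-event denominator is unstated.
- **That the second elimination rule contradicts Study limitations**, which concede that "it is not possible to prohibit all children from participating in other educational or behavioral interventions". The rule concerns interventions that could affect the results, and the limitation concerns educational and behavioural ones. The two can coexist, though the boundary calls for judgement.

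The assumed gap is also large: 3 points is close to the whole planning difference of 7.5 − 4.27 = 3.23. A removal rate of 20% is double the stated shedding rate.

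**Conclusion.** The point holds as worded in the heading. The criteria act on events after randomisation, at least two of them can in practice reach only the Tuina arm, and nothing in the article keeps the affected children in the comparison. Followed as written, they would replace the randomised comparison with a selected one.

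The direction is likely, not certain: it favours Tuina if removed children would have improved less than average. With 10% of the Tuina arm removed and an assumed 3-point deficit, the cost is 0.3 CARS points and a two-sided error of about 10% instead of 5%. These are scenarios, and no removal rate by arm or deficit stands in the article. The case for correction rests on the wording of the rules, not on these figures.

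**What to change.** 1. State that exclusion criteria arising during the study, the elimination criteria and the drop-out criteria do not determine the analysis set.
2. Make the primary analysis all randomised children in the arm assigned.
3. Seek CARS at both planned time points (after the 30-session course and at 6 months) whatever number of sessions was received. For a child who stops early, use the date on which the 30th session would have been due.
4. Keep 30-session completers as a per-protocol sensitivity analysis, and say whether the threshold applies to controls and to which sessions.
5. Count children with skin breakdown in both the numerator and the denominator of their arm's adverse-event rate. Events are already to be recorded, so this is a clarification.

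Whether treatment stops in any of these children is a clinical matter, and this change leaves it as it is.

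The cost is a change of wording and the rating of early stoppers at visits already scheduled. The estimated effect may come out slightly smaller.

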#### Drop-out criteria

1. Children experiencing adverse events during the trial, such as pneumonia and skin disease, and who could not adhere to the Tuina therapy.

2. Children whose guardian perceived the treatment as ineffective and therefore terminated the treatment.

3. Children withdrawing from the treatment at the original rehabilitation institution or after being transferred to a different rehabilitation institution.

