### Interventions

#### Control group

Based on the training of the autism organization mentioned above in this protocol, the control group will strictly follow the five schedule sessions of applied behavior analysis training, five key skill training sessions, five music group training sessions, five oral muscle training sessions, and five sensory training sessions per week. Only teachers with a background in special education will participate in the study.

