#### Tuina group

The Tuina group will receive a total of 30 sessions of pediatric Tuina (five sessions per week for 6 weeks, and a follow-up session at the 12th week after the end of treatment). From the perspective of humanistic care, to make the child feel safe, the child will be held by the parents or relatives during the session and placed in a sitting position. Tuina will be performed face to face. When performing acupoint Tuina on the back, the child will lie on his parents or relatives in a prone position.

To standardize the Tuina manipulation, only certified Chinese medicine physicians with 3 months of training in Tuina techniques will perform the procedures. The acupoint prescriptions are mainly based on the TCM theory of the relationship between *Du Meridian* and the *Brain*. After gathering clinical evidence and soliciting the opinions of experienced Tuina experts, we have summarized the following acupoints and manipulation times of Tuina. Table 1 presents the detailed information.

**Table 1 Tab1:** Tuina acupoints, manipulation times, and methods

Acuponits	Location	Methods	Times
Tianmen	Located from the middle of the eyebrows to the front hairline in a straight line	Linear-pushing with the finger	24
Kangong	Located on a horizontal line connecting both brows	Wiping with the finger	24
Taiyang (temple)	Flat part at each side of the forehead	Pressing-kneading with the finger	24
Wangu (GB12)	Located in the posterior inferior depression of the mastoid behind the ear and above the attachment of the sternocleidomastoid muscle		24
Yamen (GV15)	Located on the nape, 0.5 Cun above the middle of the posterior hairline, and below the first cervical vertebra.		100
Fengfu (GV16)	Located on the nape, when the posterior hairline is straight up 1 Cun, the extraoccipital protuberance is straight down, and the depression between the trapezius muscles		100
Baihui (GV20)	Located on the head, 5 Cun above the middle of the front hairline.		100
Shuigou (GV26)	Located on the face, at the intersection of the upper 1/3 and middle 1/3 of the sulcus		100
Du Meridian	Located on the midline of the back. Tuina therapy is mainly performed from the thoracic spine to the sacral spine.	Pressing-kneading with the finger	20
		Pinching with the finger	20
		Pushing with the finger	300
Jianjing (GB21)	Located under the spinous process of the seventh cervical vertebra, on the midpoint of the line with the acromion	Grasping with the finger	10

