### Allocation

A computer-generated random number table will be used by statisticians otherwise not involved in the study. After completing the basic data assessment of all children with ASD, the children will be randomly assigned to the Tuina and control groups in a 1:1 ratio. The treatment sequences will be provided to each Tuina physician in an opaque envelope, and only the Tuina physician will be aware of the grouping. The third-party assessors as well as the data analysts will not be aware of the treatment allocations.

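### Several rules remove children after randomisation for treatment-related reasons, and no visible text keeps them under assessment, so CARS outcomes may be lost differently between arms

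*Protocol article*

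**What the plan says.** Under Allocation, randomisation follows baseline: "After completing the basic data assessment of all children with ASD, the children will be randomly assigned to the Tuina and control groups". No trial period of Tuina before randomisation is described.

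The Eligibility criteria section then lists these rules:

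- Drop-out criteria, item 1: "Children experiencing adverse events during the trial, such as pneumonia and skin disease, and who could not adhere to the Tuina therapy".
- Exclusion criteria, second item: "Children who during the study develop conditions like phlebitis, open wounds, and skin breakdown in the manipulated area".
- Exclusion criteria, first item: "Children who are resistant to the Tuina intervention, with persistent crying and inability to adapt".
- Elimination criteria, item 1: "Children who do not complete 30 intervention sessions following the research protocol".
- Drop-out criteria, item 2: a guardian judges the treatment ineffective and ends it.
- Two more rules, on other interventions received and on leaving or changing institution, can apply in either arm.

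On dose, the Tuina group section says "The Tuina group will receive a total of 30 sessions of pediatric Tuina", at five a week for 6 weeks. The control group section lists five kinds of training at five sessions each per week, the last being "five sensory training sessions per week".

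On timing, Study design says "the participants will be evaluated again after the 30th treatment", and Primary outcomes ties the assessment to the same session count. Follow-up is 6 months after treatment. The schedule in Fig. 2 is not shown in the text available.

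**The concern.** A rule that depends on what happens during treatment removes children who have already been randomised. If it can be met in only one arm, or is met more often in one arm, the children left are no longer the groups that randomisation formed.

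Assessment timing adds to this. If the primary CARS score is due only once session 30 is done, a child who stops earlier has no due date in the visible text. A later analysis plan can define who is analysed, but it cannot supply a CARS score that was never taken. The trial is open-label, so a guardian's judgement that treatment is not working may also differ by arm. At stake is a biased treatment difference, mainly if the true effect is nil or small.

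**Working it through.** **1. Which rules act after randomisation, and in which arm**

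| Rule | Acts after randomisation? | Arm |
|---|---|---|
| Drop-out 1 (adverse event and unable to adhere to Tuina) | Yes, worded as during the trial | Tuina only |
| Skin item | Yes, worded as during the study | Tuina only in practice; controls have no manipulation |
| Exclusion 1 (resistance) | Only if applied once Tuina has begun; carries no timing | Tuina only in that case |
| Elimination 1 (30 sessions) | Yes | May be either |
| Drop-out 2 (guardian judges treatment ineffective) | Yes | Either; outcome-related |

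**2. The 30-session count**

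Tuina: 5 × 6 = 30, which reproduces the stated total. Each control training also gives 5 × 6 = 30 over 6 weeks, although the control section names no 30-session course. Elimination 1 can therefore be read as covering both arms. (The Fig. 1 caption gives two sessions a week for 6 weeks, or 12 in all; the Tuina group section is used here.)

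Because 5 × 6 is exactly 30, one missed session triggers the rule unless it is made up. Make-up sessions are not described, and may exist. If there are none and misses are independent with probability p (an assumption), the share missing at least one is 1 − (1 − p)^30:

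- p = 0.35%: 10.0%, equal to the planned shedding rate
- p = 0.5%: 14.0%
- p = 1%: 26.0%, or 52 of 200
- p = 2%: 45.5%

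Clustered misses would remove fewer children.

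**3. Illustrative bias**

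From Sample size estimation: SD 4.43, 200 per arm, 10% shedding (not split by arm), initial-study difference 7.5 − 4.27 = 3.23. The plan gives no figure for differential loss, so the rest is assumed: no true effect; a share r of children affected (2–10%); their CARS improvement d points less than the others' (0–3); all affected Tuina children lost; a share f of affected controls lost as well.

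- Bias = d·r·(1 − f)/(1 − r·f)
- SE = 4.43·√[1/(200(1 − r)) + 1/(200(1 − r·f))]
- P(significant, favouring Tuina) = 1 − Φ(1.96 − bias/SE)

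With d = 3:

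| r | f = 0 | f = 0.5 | f = 1 |
|---|---|---|---|
| 2% | 0.06; 3.4% | 0.030; 2.9% | 0; 2.5% |
| 5% | 0.15; 5.2% | 0.077; 3.7% | 0; 2.5% |
| 10% | 0.30; 9.7% | 0.158; 5.3% | 0; 2.5% |

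For r = 10%, f = 0: 3 × 0.10 = 0.30; SE = 4.43·√(1/180 + 1/200) = 0.455; 1 − Φ(1.96 − 0.659) = 9.7%.

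The sign can reverse. If affected children would improve 3 points more (d = −3, r = 10%, f = 0), the bias is −0.30 and the probability 0.4%. Swapping the arms gives the same result: if only controls are lost, for instance through drop-out 2, and they would have improved 3 points less, the bias is again −0.30.

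**4. Scale**

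0.30/3.23 = 9.3% of the initial-study difference. With 200 per arm the SE is 4.43·√(2/200) = 0.443, and 3.23/0.443 = 7.29, so power at that difference stays above 99.9%. The problem is bias, not power.

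**The case against.** A reader might infer more than the text supports, and the case against those stronger readings is good.

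- **That three rules are certainly Tuina-only after randomisation.** Exclusion 1 sits under eligibility and carries no during-study wording, unlike the item after it. It could be a screening judgement. A control child can also have a wound on the body areas in Table 1, so the skin item is Tuina-only in practice, not by definition. Only drop-out 1 names Tuina adherence outright.
- **That early stoppers have no assessment point.** Fig. 2 carries the schedule and may give week-based visits. What stands is that the visible text ties the assessment to session 30.
- **That removed children are not assessed.** No sentence says so. Elimination and drop-out could mean stopping treatment or leaving an analysis set. The loss is inferred from those words and the session-based timing.
- **That loss is probably unequal, to Tuina's advantage.** Drop-out 2 is outcome-related and, in an open trial, could remove mainly controls. Net imbalance is possible but not shown to be probable, and its direction is not known.
- **That the 30-session rule will remove many children.** Counting by session fits equally well with continuing until 30 are done, and the miss rates are assumed.

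The absence of a named analysis set is no fault here, since that may be left to an analysis plan. What remains is that the protocol itself states the removal rules, and the visible text does not say that stopping treatment leaves assessment in place. A later plan cannot repair uncollected scores.

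**Conclusion.** The point stands in limited form. Several stated rules take randomised children out for treatment-related events. One is explicitly Tuina-only, one is so in practice, one is so if applied after Tuina starts, and two depend on adherence or perceived outcome in either arm. CARS outcomes may therefore be lost differently between arms.

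Direction and size cannot be read from the documents. Under no true effect and the assumed ranges, the bias runs from 0 to about 0.3 CARS points either way, with a chance of a significant result favouring Tuina between 0.4% and 9.7% against a nominal 2.5%. It is zero if affected children are lost equally from both arms, or if they would have improved as much as the rest. The 10% ceiling assigns all planned shedding to these rules, although it must also cover transfers and other withdrawals. Equally, 0.3 is the edge of the assumed range and not a proven bound. The matter is important if the true effect is nil or small, and minor if the 3.23-point difference is real. The change should be made; confidence is medium.

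**What to change.** - Reword drop-out 1 and 2, elimination 1, the during-study skin item and any use of exclusion 1 after randomisation as reasons to pause or stop treatment, not to leave the trial. When to pause or stop stays with the investigators.
- Assess CARS and ATEC in both arms at the end of week 6 and 6 months later, whatever number of sessions was completed, unless consent is withdrawn. If Fig. 2 already sets week-based visits, say so in the text.
- Make the comparison of all children in their randomised arm primary, with 30-session completers as supportive.

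Cost: a wording amendment with ethics approval and a registry update, as the Protocol amendments section requires. Trial status reports that recruitment has ended and the intervention phase is starting, so the change is best made before outcome assessments. At 10% shedding the existing assessors would see up to 20 children × 2 arms × 2 time points = 80 extra assessments, if families can still be reached. At 1% independent misses without make-up sessions it would be 52 × 2 × 2 = 208. The estimated Tuina effect may become smaller.
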